### Immunisation program impacts

In Australia, the prevalence of the HPV types in women aged 18 to 24 years old which were targeted by the vaccine declined significantly from 28.7% in the pre-vaccination era (2005-2007), to 2.3% in vaccinated women after vaccine introduction (2010-2012).
^
5
^ The rate of high-grade cervical disease has also declined dramatically, by 2014 it dropped to less than half the 2007 rate in women under 20 years of age.
^
5
^ The introduction of the Gardasil 9 vaccine is expected to prevent up to 90% of cervical cancers. Some research suggests that increased HPV vaccination, together with greater participation in screening, has the potential to eliminate cervical cancer in Australia and elsewhere within a few decades.
^
5,
6
^

In Australia, young Aboriginal and Torres Strait Islander (hereafter, respectfully, Aboriginal) people do not receive their HPV vaccine dose, resulting in missed opportunities to be protected from HPV-related cancers.
^
4
^ This is particularly important as rates of cervical cancer in Aboriginal women are twice those of non-Indigenous women, mortality rates more than three times higher, and screening participation rates lower.
^
6–
9
^ The recent change to one HPV dose will have substantive impact on meeting the recommended dose proposed by WHO.
^
4
^ In 2022, the Australian national rate of having at least one dose of HPV vaccination for young people turning 15 years old was 83.0% for Aboriginal females and 78.1% for Aboriginal males.
^
10
^ In Western Australia (WA), the completion rates were 81.4% of Aboriginal females and 78.6% of Aboriginal males. Despite these overall rates being reasonable, there are pockets of concern within Western Australian, including the capital of the State, Perth. In 2022, 51% of Aboriginal young people in Perth received one dose of HPV vaccine during Year 7 and this did not improve in 2023 (unpublished data).
^
11
^ Substantive resources are needed to improve these rates both in school catch-up programs and within the community. To eliminate cervical cancer, improving HPV vaccine rates amongst young Aboriginal people is necessary.

Despite the decline in HPV, there are a number of reported barriers associated with HPV vaccine uptake including adolescents’ lack of awareness and knowledge, not feeling informed, and parental concerns around sexual activity and vaccine safety.
^
12

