**Outcomes**

The primary outcome, as defined by the World Health Organization and for reporting Australian reporting standards as a recipient of the HPV vaccination by the age of 15 years (ie before their 15
^th^ birthday).
^
37
^ Secondary outcome will be the number of young people who are the recipient of the HPV vaccination at 25 years old.
^
37
^

For Influencer analytics we will measure total number views, total likes, comments, and total shares. From our own social media platforms we’ll report on the average time each video was watched, whether a video was watched in full (percentage of viewers who watched the entire video), the source of where people found the videos and where the viewers were located.

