**Sample size**

Based on data from the Australian Bureau of Statistics, we anticipate approximately 89 Aboriginal youth turning 15 years old each month in Perth over the study period.
^
32
^ Using the primary outcome definition, monthly numbers of young people before their 15
^th^ birthday fully vaccinated against HPV, will be the unit of aggregation in the regression models. A total of 72 monthly data points (2020-2025) will provide 85% power to detect a one-standard-deviation shift in the average proportions post-intervention, at an α = 0.05 and a first-order autoregressive model with autocorrelation of 0.3.
^
38
^ Empirical research has shown autocorrelations of the order of 0.3 (median 0.33; IQR 0.03, 0.58; 36 ITS studies in public health).
^
39
^

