**Data analysis**

*Interrupted time series*

A linear, segmented interrupted time series analysis will be used to evaluate the impact of the social media programme on HPV vaccination.

For the primary outcome, we will count the number of youths aged between 12 and before their 15
^th^ birthday who have received the HPV vaccination per month. Similarly, for the secondary outcome, we will count the number of young people aged up to 25 (inclusive) who have received the HVP vaccination per month. Our analysis models will include two segments: a pre-interruption period of 49 months, beginning on Jan 2020-Dec 2023, and a post-interruption period of 24 months, beginning on Jan 2024-Dec 2025, which encompasses both the intervention and post-intervention periods.

For each outcome, we will fit the following statistical model (Model 1), separately for the intervention and control series:

$$\text{Model}\;1:\log Y_{t}=\beta_{0}+\beta_{1}t+\beta_{2}I+\beta_{3}\left(t-T_{I}\right)I+\text{seasonal}+\text{offset}+\epsilon_{t}$$
where

$Y_{t}$
 is the outcome value at time t, and

$T_{I}$
 is the time of the interruption. The variable

I
 indicates the post-interruption segment, which is equal to 1 post the interruption and 0 before. Parameter

$\beta_{0}$
 is the intercept at the beginning of the series,

$\beta_{1}$
 is the slope in the first segment,

$\beta_{2}$
 is the level change between the expected value (based on the pre-interruption data) and the observed data, and

$\beta_{3}$
 is the difference in slope compared to

$\beta_{1}$
. The error term,

$\varepsilon_{t}$
 represents deviations from the fitted model, and we will assume these to have lag-1 autocorrelation. Seasonality will be accounted for by including two pairs of sine and cosine harmonics with periods of 12 and 6 months.
^
40,
41
^ Due to the changing of the vaccine schedule in the year following the interruption, the seasonal components will be phase shifted by six months for that year. The log of the relevant population (i.e. all Aboriginal youth aged between 12 and before their 15
^th^ birthday per month) will be included as an exposure offset to adjust for any changes to the population over time. We will assume a negative binomial distribution with a log link function. We will fit these models using the glarma package in R.
^
42
^

The effect measures of interest will be:

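### The negative binomial model on the 12-to-under-15 population does not match the primary outcome as defined and sized, which is a monthly proportion vaccinated by the 15th birthday

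*Protocol article*

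**What the plan says.** All references are to the protocol article.

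- **Outcomes.** The primary outcome is defined "as a recipient of the HPV vaccination by the age of 15 years". This is a yes/no status for each person, fixed at the 15th birthday.
- **Sample size.** The section states "we anticipate approximately 89 Aboriginal youth turning 15 years old each month in Perth". It adds that the monthly number of under-15s "fully vaccinated against HPV, will be the unit of aggregation in the regression models". The stated power, 85% from 72 monthly points at α = 0.05 with autocorrelation 0.3, is power to "detect a one-standard-deviation shift in the average proportions post-intervention".
- **Data analysis.** The outcome becomes a monthly count of vaccinated youths aged 12 up to the 15th birthday. The offset is the log of everyone in that age band. The model has trend, level-change and slope-change terms, harmonics of 12 and 6 months with a six-month phase shift in one year, and lag-1 autocorrelation. The distribution is fixed: "We will assume a negative binomial distribution with a log link function".
- **Coverage.** Under Immunisation program impacts, for Western Australia, "the completion rates were 81.4% of Aboriginal females and 78.6% of Aboriginal males". The national at-least-one-dose rates at 15 are 83.0% (females) and 78.1% (males). The Discussion gives national full-course rates of 75% and 68%. The only Perth figure is 51%, for one dose during Year 7.

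**The concern.** Outcomes and Sample size describe a bounded count: so many vaccinated out of a cohort of about 89. Data analysis describes an event count over a much larger population at risk. The article does not say which one the primary model takes as its response.

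This matters because the two need different variance functions. A negative binomial has variance mean + mean²/θ, which is never below the mean. A count of successes out of a known cohort with most members vaccinated has variance well below its mean. If the stated family is used for the declared outcome, the dispersion sits at its limit, the intervals are too wide, and a real rise in coverage by 15 may be reported as no effect. If the model is instead used as Data analysis most naturally reads, the primary analysis estimates something that was neither defined nor sized.

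**Working it through.** **1. The plan's own figure.** Take a shift in mean between 48 and 24 months, lag-1 autocorrelation 0.3 and two-sided α = 0.05. Generalised least squares gives a standard error of 0.332 SD. Then 1/0.332 − 1.96 = 1.05, and Φ(1.05) = 85%. The stated power reproduces as a plain shift in a monthly proportion. It does not draw on the negative binomial model or the 12-to-under-15 offset.

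**2. Variance for the declared outcome.** Inputs: n = 89 (Sample size) and p = 0.80 (midpoint of 81.4% and 78.6%, a state figure).

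- Mean: np = 89 × 0.80 = 71.2
- Binomial variance: np(1−p) = 71.2 × 0.20 = 14.24
- Smallest variance a negative binomial allows: 71.2
- Ratio of standard errors: sqrt(71.2/14.24) = sqrt(5) = 2.24, which is 1/sqrt(1−p)

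At the other rates in the article:

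| p | source | 1/sqrt(1−p) |
|---|---|---|
| 0.51 | Perth, Year 7 only | 1.43 |
| 0.68 | national full course, males | 1.77 |
| 0.75 | national full course, females | 2.00 |
| 0.786 | WA males | 2.16 |
| 0.814 | WA females | 2.32 |
| 0.83 | national one dose, females | 2.43 |

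**3. Simulation.** Settings: 72 months, a fixed cohort of 89, Model 1's eight mean terms, the negative binomial at its Poisson limit, no autocorrelation. The ratio of model standard error to true SD of the level change was about 2.2 at 80%, 1.8 to 1.9 at 70% and 1.4 at 51%. At 80% with no effect, false positives were 0.0% to 0.1%, against 4.4% to 4.5% for a quasi-binomial model. Power for a step from 80% to 88% was 25% to 27%, against 99% for quasi-binomial. For 80% to 86% it was 3%, against 81% with a dispersion-scaled standard error.

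**4. Extra month-to-month variation.** Let true coverage vary with SD s (an assumption). The variance is np(1−p) + n(n−1)s². For s = 0.04 this is 14.24 + 89 × 88 × 0.0016 = 26.77, and the ratio is sqrt(71.2/26.77) = 1.63 (1.70 simulated). For s = 0.02 it is 2.02 and for s = 0.06 it is 1.30. It reaches 1 at about s = 0.085.

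**5. Varying cohort, smooth offset.** Suppose the number turning 15 is Poisson with mean 89 (an assumption) and the offset is a smooth population estimate. The vaccinated count is then itself Poisson, with variance 71.2. The simulated ratio is 0.98 to 1.00 and the error rate 5.5% to 5.7%, so the test is valid. Most of the noise, however, is cohort size, which a known denominator would remove. Power for 80% to 88% is about 41%, against 99% for a binomial model using each month's actual number turning 15.

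**6. New vaccinations per month.** The 12-to-under-15 population is about 36 × 89 = 3,204 (assuming equal monthly cohorts). With 45 to 300 new vaccinations a month (assumed), the monthly rate is 1.4% to 9.4% and 1/sqrt(1−rate) is 1.01 to 1.05. Here the negative binomial is suitable.

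**The case against.** The strongest reply is that the negative binomial is never paired with the cohort of 89. Data analysis attaches it to a monthly count on the whole 12-to-under-15 population. Read as new vaccinations, the family fits (step 6). The harmonics and the phase shift for a changed vaccine schedule also make most sense for doses by calendar month. This stands, and it means the variance problem cannot be separated from the mismatch: if the authors declare new vaccinations as the outcome, it disappears. It does not remove the mismatch, because Sample size ties the regression models to the before-15 outcome. Data analysis can also be read as the number in the age band already vaccinated, which is again a bounded, high-proportion count.

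A second reply is that 80% is a state-wide rate, which the article contrasts with Perth. This stands as a limit on the size. The 51% is Year 7 uptake, though, not coverage by 15, and no by-15 rate for Perth is given.

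A third is that a step from 80% to 88% means reaching 8/20 = 40% of those otherwise unvaccinated, at once and in every later cohort. That is fair. The step is an illustration, not an expected effect.

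Finally, a change of family does not cure everything. Youths aged 12 when the campaign began in February 2024 turn 15 from February 2026, after the series ends. That is a separate limitation.

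**Conclusion.** The point holds as a mismatch with a conditional statistical cost. The outcome defined and sized is a proportion of those turning 15; the model fixed in Data analysis suits new vaccinations among all 12-to-under-15s.

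If the stated family is applied to the declared outcome with the cohort turning 15 as denominator, standard errors are too wide by roughly 1.8 to 2.4 at by-15 rates of 68% to 83%. The factor would be 1.4 at 51%, and about 1.7 at 80% with a 4-point monthly SD in true coverage. With a smooth offset and a varying cohort, the error rate is about right but power is still lost.

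A reader might infer that the planned analysis will certainly give intervals 2.2 times too wide and an error rate near zero. The document does not support that. It requires about 80% coverage, a known denominator of 89 and little extra variation, and Data analysis names a different offset. The simulations omitted autocorrelation and did not use the planned glarma package, so the figures show order of magnitude.

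**What to change.** Decide which quantity is primary and make Outcomes, Sample size and Data analysis agree.

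For the outcome as defined, replace the distribution sentence with wording such as: the number vaccinated before the 15th birthday, out of those turning 15 in month t, will be modelled as binomial (quasi-binomial or beta-binomial if over-dispersed) with a logit link and that month's number turning 15 as denominator. Keep the segments and the lag-1 term, and drop the population offset. Re-justify the harmonics and the six-month phase shift for a series indexed by month of 15th birthday, since they were chosen around the vaccination calendar.

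Keep the negative binomial with the 12-to-under-15 offset only for a separately named outcome of new vaccinations per month.

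The cost is small. It is a change of wording, family and denominator, and Data collection already requests dates of birth and vaccination timing. The downside is that effects are reported as odds ratios or percentage points instead of rate ratios. The software must also handle a binomial-type response with lag-1 dependence.

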•Level change at the end of the social media campaign (i.e. three months post the beginning of the social media campaign).•Change in slope.

In addition to the above model, for both outcomes, we will also fit the following single model (Model 2) that incorporates both the intervention and control series:

$$\text{Model}\;2:\log Y_{t}=\beta_{0}+\beta_{1}t+\beta_{2}I+\beta_{3}\left(t-T_{I}\right)I+\beta_{4}G+\beta_{5}\mathrm{tG}+\beta_{6}\mathrm{IG}+\beta_{7}\left(t-T_{I}\right)\mathrm{IG}+\text{seasonal}+\text{offset}+\epsilon_{t}$$
where

$Y_{t},T_{I},I,t,\text{seasonal},\text{offset and}\;\epsilon_{t}\;$
are as described above.

G
 represents the series with a value of 1 representing the intervention series, and a value of 0 representing the control series.

$\beta_{0}$
,

$\beta_{1}$
,

$\beta_{2}$
 and

$\beta_{3}$
 are as described above for the control series.

$\beta_{4},\beta_{5},\beta_{6}\;\text{and}\;\beta_{7}$
 represent the interactions between time and the intervention series. Specifically,

$\beta_{4}$
 represents the difference in the intercept at the beginning of the series between the intervention and control series,

$\beta_{5}$
 represents the difference in slope between the intervention and control series in the first segment,

$\beta_{6}$
 represents the difference in the level change between the intervention and control series, and

$\beta_{7}$
 represents the difference in the change in slope between the intervention and the control series.

We will compare the estimates of level change at the end of the social media campaign and change in slope between Model 1 and Model 2. This comparison will allow us to assess the possibility of whether a co-intervention/concurrent event may explain our findings.
^
35
^

We will plot interrupted time series graphs for all outcomes and series using the recommendations of Turner et al.
^
43
^ These plots will include: data points, trend lines, seasonality estimation and confidence intervals surrounding the trend line and counterfactual estimates. Segments will clearly delineated by breaks in the trend lines.

Subgroup analysis

We will fit Model 1 for the primary and secondary outcomes for the intervention series separately by:
•Sex (Females, Males)•Location in Perth (North West, North East, Central, South West and South East)

Influencer data

All qualitative information will then be synthesised descriptively, key messages will be identified, with thematic analysis completed using Nvivo software.

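### The primary outcome is coverage by the 15th birthday, but the planned monthly count, level change and slope change cannot reliably separate doses brought forward from coverage gained

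*Protocol article*

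**What the plan says.** Under Outcomes, the protocol article defines the primary outcome as being "a recipient of the HPV vaccination by the age of 15 years", that is, before the 15th birthday. The Sample size section matches this: about 89 Aboriginal youths turn 15 each month in Perth, and the power statement concerns a shift in average proportions.

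The Data analysis section fixes something different. For the primary outcome, "we will count the number of youths aged between 12 and before their 15"th birthday who have received the vaccine per month. The offset is "The log of the relevant population (i.e. all Aboriginal youth aged between 12 and before their 15"th birthday. The effect measures are the "Level change at the end of the social media campaign (i.e. three months post the beginning of the social media campaign") and "Change in slope". Model 2 adds the non-Aboriginal series. The secondary outcome is also a monthly count. No measure follows a cohort to age 15, and doses brought forward are not discussed.

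Under Immunisation program impacts, the article reports that in 2022 "51% of Aboriginal young people in Perth received one dose of HPV vaccine during Year 7", and that in Western Australia "the completion rates were 81.4% of Aboriginal females and 78.6% of Aboriginal males".

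**The concern.** The aim is higher coverage by 15. A monthly count over ages 12 to under 15 rises when more young people are vaccinated, but also when the same young people are vaccinated sooner. The campaign is timed to school consent, the school dose and the catch-up program, so it acts when later doses can move earlier. The introduction describes free catch-up for those who miss the school dose, so such later doses exist.

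If doses move earlier within ages 12-14, coverage by 15 is unchanged, yet the planned analysis could show a positive level change. The trial might then report improved vaccination rates, and the Dissemination section plans wider use of the model on that basis.

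**Working it through.** **The plan's own figure.** The 85% power reproduces. Inputs: 48 pre and 24 post months (January 2020 to December 2023 is 48 calendar months), lag-1 autocorrelation 0.3, two-sided alpha 0.05, shift of 1 SD. For a plain mean shift the generalised least squares standard error is 0.332 SD, so power = Φ(1/0.332 − 1.96) = 85.4%. That figure fits a shift in the average proportion vaccinated, not the level and slope terms of the segmented count model.

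**Scenario fits.** Model 1 (level, slope, 12- and 6-month harmonics, constant offset) was fitted to noise-free expected monthly doses and compared with a no-campaign fit. Assumptions:
- school-year cohorts of 1,000, with 51% vaccinated in Year 7 in a seasonal pattern;
- a further 29% vaccinated later, spread over 12 or 24 months, evenly or front-loaded;
- Year 7 uptake raised by 5 points, with 0%, 59% or 100% of the extra doses taken from that cohort's later doses.

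The level change is exp(β2 + 3β3) − 1; the yearly slope change is exp(12β3) − 1.

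| Uplift in 2024 cohort only | Level at 3 months | Slope per year | Final gain by 15 | Net excess to Dec 2025, per 1,000 |
|---|---|---|---|---|
| 0% displaced | +6% to +7% | about −5% | 5.0 points | 50 |
| 59% displaced | +6% to +8% | −6% to −9% | 2.0 points | 20-35 |
| 100% displaced | +6% to +8% | −8% to −11% | 0 points | 0-25 |

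Within any one catch-up pattern the level change varies by less than 1 percentage point across the three rows. If the uplift is sustained in the 2024 and 2025 cohorts, the slope change is about 0% per year for a true gain and −3% to −6% when fully displaced. The level change is again about 6% to 7%.

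**Can the slope separate them?** The gap between full gain and full displacement is 3 to 6 points per year in both cases. At 89 youths per month the expected monthly count is 0.51 × 89 = 45.4 or 0.80 × 89 = 71.2. With Poisson variance and autocorrelation 0.3, the standard error of the 12-month log slope is 0.074 or 0.059. An assumed monthly log-rate SD of 0.15 gives about 0.075 to 0.08, and overdispersion makes it larger. The gap is no larger than the standard error.

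**A second construction** used monthly birth cohorts of 89 and an assumed age at dose centred 12 months after the 12th birthday (SD 5 months). A sustained true gain of 5 points gives level ratios of 1.098 (51% base, 1 + 5/51) or 1.0625 (80% base, 1 + 5/80), with slope ratio 1.000. A steady advance in timing, totalling about 2.35 or 1.5 months over the 24 months with coverage unchanged, gives 1.098 or 1.062 and slope ratio 1.000. The two measures then agree completely. If the count is read as the running total vaccinated, a permanent advance of about 2.3 or 1.5 months has the same lasting effect as a fully realised 5-point gain.

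**By-age series.** If the outcome is the number turning 15 in a month who were already vaccinated, with the number turning 15 as offset, doses moved within ages 12-14 give a ratio of exactly 1.000.

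**Control series.** Model 2 removes what is common to both groups. Displacement caused by the campaign occurs only in the targeted group, so it stays in β6 and β7.

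**The case against.** The strongest reply is that Outcomes and Sample size describe a by-age outcome, and a series of youths turning 15 would be immune to the problem. That is right as far as it goes. But the count and offset in Data analysis are explicit and do not describe that series, so the sections conflict and need reconciling whichever was meant.

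A reader might infer from the article's figures that (80.0 − 51)/(100 − 51) = 59% of those missed in Year 7 are vaccinated later anyway, where 80.0 is the mean of 81.4 and 78.6. The documents do not support that. The 51% is Perth, Year 7; the 80% is the whole state at about age 15, and so different birth cohorts. The article itself singles out Perth as a pocket of concern. The 59% is illustrative only. The argument does not need it, since the level change is nearly the same at any displaced share.

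A reader might also infer that a falling slope says nothing because it falls under a true gain too. That holds only for a gain lasting one year; for a sustained gain the slope change is about zero. The limit is precision, not that the sign never differs. The planned plots of data against the counterfactual could also show a later shortfall, but nothing quantifies it.

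Finally, the scenarios alter only Year 7 uptake, while the campaign also targets catch-up and ages 12-16. Real effects may be a mixture.

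**Conclusion.** The point stands. The analysis as written does not estimate the primary outcome as defined, and its two effect measures do not reliably distinguish earlier vaccination from higher coverage by 15. For an assumed 5-point rise in Year 7 uptake, the level change is about +6% to +8% whether the eventual gain is 5 points or none.

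This rests on the monthly-count reading of Data analysis, and on assumed values for the uplift, the timing of later doses and the variance. It does not show that displacement will occur, or how much. It shows that, if it did, the planned measures would probably report it as a gain.

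**What to change.** Reconcile Outcomes, Sample size and Data analysis on what the primary series is. Keep the monthly model if wanted, and add a by-age cohort analysis in both groups:

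- (a) the share vaccinated before the 15th birthday among those turning 15 each month, with the number turning 15 as offset;
- (b) for each Year 7 entry cohort, cumulative first-dose coverage at the end of Year 7 and at 24 months after entry, as the 2024-versus-earlier difference relative to controls, with confidence intervals.

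Report cumulative net excess doses to December 2025 (observed minus counterfactual) beside the three-month level change. Describe a level change without a by-age coverage gain as earlier vaccination or as unresolved, and do not claim improved coverage by 15 from the level change alone.

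The cost is revised wording and some added tables; date of birth and vaccination timing are already in the register request.

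The added analysis has limits. By December 2025 only part of the exposed cohorts will have turned 15, and the 2024 Year 7 cohort will be about 14. In the second construction, about 2.7 of a true 5 points would be visible by then. With 89 × 12 = 1,068 youths per cohort and three earlier cohorts (3,204), the standard error at 75% coverage is √[0.75 × 0.25 × (1/1,068 + 1/3,204)] = 1.5 points, before control-group and between-year variation. A 2-point gain would be about 1.3 standard errors. Net excess overlaps between 59% and full displacement (20-35 against 0-25 per 1,000), so those two may not be fully separable. The report should say so.

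### Model 2 has one seasonal term for both groups while Model 1 lets seasonality differ, so comparing the two models also tests an unstated equal-seasonality restriction

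*Protocol article*

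**What the plan says.** All of this is in the Data analysis section of the protocol article.

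- Model 1: "For each outcome, we will fit the following statistical model (Model 1), separately for the intervention and control series".
- Its seasonal part: "Seasonality will be accounted for by including two pairs of sine and cosine harmonics with periods of 12 and 6 months". For the year after the interruption, because the vaccine schedule changed, "the seasonal components will be phase shifted by six months for that year". No distinction by group is made.
- The joint model is introduced with the words "for both outcomes, we will also fit the following single model (Model 2) that incorporates both the intervention and control series". Its seasonal term is defined by reference back to Model 1. The group coefficients β4 to β7 "represent the interactions between time and the intervention series". They are then listed one by one as differences in intercept, pre-interruption slope, level change and slope change. The equation has no product of group and season.
- Use of the two models: "We will compare the estimates of level change at the end of the social media campaign and change in slope between Model 1 and Model" (the joint one). The stated purpose is to assess whether a concurrent event could explain the findings.

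**The concern.** Separate fits of Model 1 estimate four harmonic coefficients per series, eight in all. Model 2 as written estimates four. Moving from Model 1 to Model 2 therefore changes two things at once: the control series enters, and the two groups are made to share one relative seasonal pattern. If the models disagree, the plan reads this as information about co-interventions, but part of the disagreement may come from the seasonal constraint.

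The outcome is a monthly vaccination count in a programme delivered mainly through schools, so a marked seasonal swing is to be expected. Catch-up doses may be given at school, at health centres or by general practitioners, so the groups could have different swings. Equal seasonality is thus a real restriction, and the plan neither states nor checks it. At stake is the controlled contrast (β6 and β7), which is why a control series is included.

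**Working it through.** **Is there a figure to reproduce?** The plan gives none for seasonality. Its one design figure, 85% power with 72 monthly points and autocorrelation 0.3, reproduces for a simple mean shift (85.4% with 48 + 24 months, 84.6% with 49 + 23, two-sided). It does not bear on this point.

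**How the bias arises.** Write S(t) for the four harmonic terms and δ for the group difference in their coefficients. The log ratio of intervention to control is then

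β4 + β5·t + β6·I + β7·(t − T_I)·I + δ′S(t).

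Model 2 omits δ′S(t). Whatever part of it the segment terms (1, t, I, (t − T_I)·I) can mimic is credited to β4–β7. The rest stays in the residual.

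**Inputs from the article.** 72 months per series (144 observations), negative binomial with log link, harmonics of 12 and 6 months, and a six-month phase shift, applied here to calendar 2024. The article states segments of 49 and 24 months, which sum to 73, while its dates give 48 + 24 = 72. Both 48/24 and 49/23 were therefore run.

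**Inputs that are assumptions.** Control 12-month log-amplitude 1.0, and intervention 0.7 or 0.5. In peak-to-trough terms these are exp(2 × 1.0) = 7.4, exp(2 × 0.7) = 4.1 and exp(2 × 0.5) = 2.7. Monthly means are about 900 and 60, and dispersion is 0.1. True β6 = β7 = 0.

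**Method.** Model 2 was fitted to noise-free means, with the control peak placed in each calendar month in turn.

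| Intervention amplitude | Split | False β6 ratio over peak months |
|---|---|---|
| 0.7 | 48/24 | 0.93 to 1.08 |
| 0.7 | 49/23 | 0.89 to 1.12 |
| 0.5 | 48/24 | 0.89 to 1.13 |
| 0.5 | 49/23 | 0.82 to 1.21 |

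For a March, May or September peak at amplitude 0.7, the ratios are 0.93, 0.95 and 1.07 (48/24) or 0.90, 0.99 and 1.11 (49/23). The direction and size thus depend on the peak month, and some months give almost no bias.

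**Where the seasonal difference goes.** For a 12-month difference with the planned shift, the segment terms absorb only 0 to 3% of its variance. The remainder enters the autocorrelation and dispersion estimates. For differences of 0.2 to 0.5 log units in any phase, |β7| reaches at most about 0.006 per month. For a difference of 0.5, the controlled level change three months in, β6 + 3β7, is off by up to 0.14 (48/24) or 0.20 (49/23) on the log scale, similar to β6.

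**With group-by-seasonal terms added.** The false β6 and β7 are zero to numerical precision in every scenario. The standard error of β6 rises from 0.230 to 0.233, and 0.233/0.230 = 1.013.

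**The case against.** The strongest reply has four parts.

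1. **No evidence of different seasonality.** This stands. A reader might infer a flatter pattern in the intervention group from the statement that "In 2022, 51% of Aboriginal young people in Perth received one dose of HPV vaccine during Year 7" set against the statewide Aboriginal figures by age 15 (81.4% of females, 78.6% of males). Those figures differ in place and birth cohort, and no coverage or timing figure is given for the non-Aboriginal control group. They cannot show how many doses are catch-up, or that the groups' seasonal swings differ.

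2. **A seasonal difference does not pass wholesale into β6 and β7.** This also stands. Over segments of about whole years the harmonics are nearly orthogonal to level and slope, and only a small part, depending on phase, leaks in.

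3. **Larger biases are not those of the planned model.** A reader who fits Model 2 at 48/24 without the phase shift would find β6 ratios of 0.81, 0.86 and 1.23 (March, May and September peaks) at amplitude 0.7, or 0.71, 0.78 and 1.41 at 0.5. The article specifies the shift, so these do not apply. On the log scale they are nearly three times too large. Nor can the bias be called as large as a plausible campaign effect, because the article states no target rate ratio.

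4. **Model 2 is supplementary, and a shared harmonic is a common economy.** This stands in part. Model 1 has group-specific seasonality, and the planned plots with seasonality estimates could reveal a misfit. But Model 2 supplies the only formal controlled contrast. Its equation and coefficient list are written out in full, so the missing interaction is not merely detail left to a longer document.

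**Conclusion.** The structural point holds: as written, Model 2 imposes equal relative seasonality and Model 1 does not, so their comparison does not isolate the control adjustment. That follows from the text and needs no assumption.

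The size is conditional. If the 12-month log-amplitudes differ by 0.3 to 0.5, with the planned phase shift in 2024, a null campaign could show a controlled level ratio anywhere from near 1 to about 7–12% off (difference 0.3) or 11–21% off (difference 0.5). The sign and size depend on the peak month and the month split. If the groups share one relative seasonal pattern, there is no bias. The documents do not show which case applies. This is a modest and avoidable weakness in the controlled analysis. It does not invalidate the design or the separate Model 1 fits.

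**What to change.** Add to Model 2 the product of G with each of the four harmonic terms, built from the same phase-shifted harmonics in the changed-schedule year. State in the analysis plan, before the register data are analysed, that seasonality is group-specific in both models. Suggested wording: Model 2 will include interactions between the series indicator and all sine and cosine terms, with the six-month phase shift applied to these terms as in Model 1.

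The mean structure of Model 2 then equals the two Model 1 fits side by side, and β6 and β7 are contrasts of level and slope change free of the seasonal constraint. The cost is one sentence, four more coefficients on 144 observations, and a standard error for β6 about 1% larger. Nothing else in Model 2 has to change for this point.
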